### Definitions of study groups

VAPOR 1 has a case–control study design, with three groups of participants: PDAC, benign conditions and healthy controls.

PDAC: participants who either have a confirmed diagnosis of PDAC according to a biopsy or tissue sample taken from the pancreas, or who are due to undergo surgical resection for suspected PDAC (with histological confirmation to follow within 3 months).

Benign pancreatic conditions: participants with either new-onset diabetes mellitus (diagnosed within the previous 6 months) or chronic pancreatitis diagnosed clinically or radiologically at any time. Diabetes mellitus is confirmed if the participant’s average circulating blood sugar level, determined by glycated haemoglobin, is greater than 48 mmol/mol at the time of diagnosis.

Negative control group: participants with a radiologically normal pancreas confirmed by abdominal imaging, ideally within the previous 12 months.

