### Sample size

The sample size of 205 PDAC cases was based on a target sensitivity of 85%, with 7% precision and 80% power, informed by pilot data on 132 patients.^10^ We aim to recruit the same number of each type of control, totalling 615 participants with complete data. Allowing for 20% attrition due to loss of samples, we will recruit 771 participants, which includes at least 256 with cancer.

Riley *et al*^11^ also recommend ensuring that the sample size achieves small mean absolute prediction error (MAPE), defined as the mean absolute difference between predicted and observed outcomes (cancer=1, no cancer=0), and large variation explained by the CPM, measured by Cox-Snell R^2^, which ranges from 0 for no predictive value to 1 for perfect prediction. Additionally, the area under the receiver-operating curve (AUC) provides an estimate of the ability of the CPM to discriminate between cancer and non-cancer cases. The resulting CPM based on 615 participants will have an MAPE of 0.048, estimate cancer incidence with precision 0.088, and achieve a minimum Cox-Snell R^2^ of 0.431 based on forty predictors. The SE in the AUC achieved by the CPM will be 0.016, based on an AUC of 0.86.

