A 10-fold CV will be used for internal validation of statistical and machine learning models. Nested CV will be applied to best identify the penalty terms in LASSO and elastic net models, as well as to fine-tune the hyperparameters in random forest and DNNs, reducing the risk of overfitting across all models. For each fold in the internal CV, the sensitivity, AUC, precision-recall AUC and the MAPE will be calculated and summarised by median (IQR) values across folds. Apparent performance with 95% CIs and optimism will be calculated by 100 bootstrap resamples. Predictors chosen in ≥50% bootstrapped selection routines will be taken forward.

For the final model, bias-corrected ROC (receiver operating characteristic) curves and calibration plots will be provided. All model coefficients with SEs, and ORs with 95% CIs will be reported.

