#### Derivation of diagnostic rules

A clinical decision rule will be derived from probabilities of PDAC generated by the final CPM, with thresholds for referral for definitive testing, review within 6 months and discharge.

Development of decision rules will consider the cost of missing a PDAC case and of incorrectly declaring PDAC in the control group. The net benefit of the CPM will be calculated across a range of candidate thresholds.^17^ We will use decision curve analysis^18^ to compare the net benefit of the proposed CPM against the current standard of care of referring all symptomatic patients. We will also consider the threshold which maximises the expected number of patients taking the test before misdiagnosis occurs, weighted by the ‘clinical cost’ of a false negative relative to a false positive.^19^ This relative ‘clinical cost’ will be elicited from expert clinicians and members of the study steering group, which includes patient representatives.

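### The referral rule and net benefit rest on probabilities from a sample that is one-third cancer by design, with no stated re-anchoring to primary-care prevalence

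*Protocol article*

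**What the plan says.** Under Definitions of study groups: "VAPOR 1 has a case–control study design, with three groups of participants: PDAC, benign conditions and healthy controls". Under Sample size, "The sample size of 205 PDAC cases was based on a target sensitivity of 85%, with 7% precision and 80% power", and then "We aim to recruit the same number of each type of control, totalling 615 participants with complete data". The analysed sample is therefore planned as 205 PDAC, 205 benign and 205 healthy.

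Under Derivation of diagnostic rules: "A clinical decision rule will be derived from probabilities of PDAC generated by the final CPM", with cut-offs for three actions (referral, later review, discharge). The section continues: "The net benefit of the CPM will be calculated across a range of candidate thresholds". A decision curve will compare the model with referring all symptomatic patients. A further threshold will maximise the expected number of people tested before a misdiagnosis, weighted by the relative clinical cost of the two kinds of error.

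The Abstract and the strengths-and-limitations box place the test in primary care, for people whose symptoms fall short of current urgent referral criteria. The Objectives include the clinical utility of the model and a comparison with current practice. The limitations box acknowledges that recruitment takes place in secondary care. It does not mention the artificial case share.

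**The concern.** Case–control sampling leaves odds ratios and ranking intact but not the intercept of a logistic model. The intercept absorbs the ratio of cases to controls that recruitment chose. A predicted probability from this model therefore answers the question of how likely PDAC is in a group where one person in three has it. That is not the question a general practitioner faces.

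Each quantity in Derivation of diagnostic rules depends on prevalence: the probability cut-offs, net benefit, the refer-all line of the decision curve, and the number tested before misdiagnosis. The planned internal validation cannot reveal the problem, because cross-validation and bootstrap resampling reuse the same one-third mix. Sample size also speaks of estimating cancer incidence from this sample, which treats a design-fixed fraction as if it could be estimated.

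What is at stake is the clinical-utility objective. The size and sign of net benefit, and the meaning of each cut-off, could be wrong for the intended users.

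**Working it through.** **Inputs from the article.** 205 cases and 615 in total; sensitivity 85%, precision 7%, power 80%; 20% attrition; AUC 0.86 with SE 0.016.

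**Assumptions not in the article.** Target prevalence π from 0.2% to 3%; an illustrative threshold pt = 2%; an equal-variance binormal score; two-sided 5% for reproducing the sample size.

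**1. The plan's own figures.**
- n = (1.960 + 0.842)² × 0.85 × 0.15 / 0.07² = 204.2, so 205.
- 205 / 0.8 = 256.25, so 257 per group, and 3 × 257 = 771.
- Newcombe's formula with N = 615, case share 1/3 and AUC 0.86 gives SE = 0.0161, against the stated 0.016.

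The planned case share is 205/615 = 33.3%, and the stated SE agrees with it.

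**2. Shift from sample to target scale.** logit(target) = logit(sample) + ln[π/(1−π)] − ln(205/410), where ln(205/410) = −0.693.

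| π | Shift | Sample odds divided by | Sample risk of 30% becomes |
|---|---|---|---|
| 3% | −2.78 | 16 | 2.6% |
| 1% | −3.90 | 49.5 | 0.86% |
| 0.2% | −5.52 | 250 | 0.17% |

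**3. A 2% cut on uncorrected probabilities.** Separation d = √2 × Φ⁻¹(0.86) = 1.528. The cut sits at log likelihood ratio ln(0.02/0.98) + 0.693 = −3.199. On the score scale this is (−3.199 + 1.528²/2)/1.528 = −1.330. Sensitivity is 1 − Φ(−1.330 − 1.528) = 0.998 and specificity is Φ(−1.330) = 0.092.

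**4. Net benefit.** NB = Se × π − (1−Sp) × (1−π) × pt/(1−pt), with pt/(1−pt) = 0.02/0.98 = 0.0204. For refer-all, Se = 1 and Sp = 0. For the recalibrated model at π = 1%, a true 2% risk lies at about 50% on the sample scale, which gives Se 0.619 and Sp 0.890.

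| Setting | Uncorrected rule | Refer-all | Recalibrated |
|---|---|---|---|
| Sample, 33.3% | 0.3203 | 0.3197 | same as uncorrected |
| π = 3% | 0.0120 | 0.0102 | 0.0193 |
| π = 1% | −0.0084 | −0.0102 | 0.0040 |
| π = 0.2% | −0.0165 | −0.0184 | 0.0002 |

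Check of one cell: refer-all at 1% is 0.01 − 0.99 × 0.0204 = −0.0102.

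**5. Other thresholds.** At π = 1%, the uncorrected, refer-all and recalibrated values are −0.016, −0.021 and +0.003 at a 3% threshold, and −0.030, −0.042 and +0.002 at 5%. The order (recalibrated, then uncorrected, then refer-all) holds for thresholds from 1% to 30% and π from 0.2% to 3%. The sign depends on the inputs: at π = 3% with a 2% threshold all three are positive.

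**The case against.** **The article is silent; it does not exclude a correction.** It does not say that the probabilities will be used uncorrected, and a full protocol or analysis plan not shown here may contain the step. That limits what can be said about intent. It does not remove the point. The article sets out the source of the probabilities, the thresholds, the comparator and the elicitation of costs, and those steps carried out as stated give absolute quantities on the wrong scale.

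**The thresholds are not fixed numerically.** This stands. A constant logit shift is monotone, so a cut-off chosen on the sample scale classifies the same people after the shift. What is at risk is the choice and meaning of the cut-off, and the net benefit attached to it.

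**Stronger readings that the documents do not support.**
- A reader might infer that the rule can never apply in primary care. It can be re-anchored from the same data.
- A reader might infer that almost everyone would be flagged. That follows only at low cut-offs: under the same binormal model, uncorrected specificity is 0.09 at 2%, 0.24 at 5% and 0.41 at 10%.
- A reader might infer that the ranking against refer-all reverses. In this example the uncorrected model stays slightly ahead of refer-all. What changes at 1% prevalence is the sign: the uncorrected rule falls below referring nobody.
- A reader might count the planned calibration plots as an error. Plots on the sample scale are legitimate internal validation.

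**The secondary-care limitation is disclosed.** It concerns the recruitment setting and the spectrum of participants. It does not tell the reader that the case share was set by design.

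**Conclusion.** The point holds. The rule, the net benefit, the decision curve and the misdiagnosis criterion are to come from a model fitted where 33.3% have PDAC by design, and the article states neither a target prevalence nor a correction. Carried out as written, absolute risks are overstated: the odds are about 16 times too high at 3% prevalence, 50 times at 1% and 250 times at 0.2%. Net benefit is then wrong for the clinical-utility objective.

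In the worked example the sample shows no visible gain over refer-all (0.320 for each). At 1% prevalence the recalibrated model is the only one of the three with positive net benefit. The exact sizes rest on the assumed prevalence, threshold and binormal shape. The direction is robust across the assumed 0.2% to 3%. AUC, odds ratios and the ordering of patients are untouched.

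**What to change.** Before model results are seen:

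1. State a target prevalence range for the intended-use population, with its source. Defining that population also requires reconciling two statements: the Abstract aims at people who do not meet referral criteria, while Derivation of diagnostic rules takes referral of all symptomatic patients as current practice.
2. Shift the model's logit by ln[π/(1−π)] − ln(cases/controls), using the counts actually analysed.
3. Derive the probability thresholds on the shifted scale.
4. Compute net benefit, the decision curve and the misdiagnosis criterion from sensitivity, specificity and π over the stated range.
5. Report specificity separately for benign and healthy controls, because their equal mix is also a design choice.
6. State that these results assume sensitivity and specificity carry over to primary care. An intercept shift does not repair differences in the spectrum of controls.

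The cost is some analysis wording and a few lines of code; recruitment, sampling and model fitting do not change. The downside is that an external prevalence must be assumed and defended, and the reported net benefit and positive predictive value will look less favourable.

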#### Developing and reporting the CPM

Initially, relationships between candidate VOCs and the presence of PDAC will be explored using univariate logistic regression models, including linear, polynomial and cubic splines.

Given the large number of initial variables, a screening step will be undertaken to identify the most promising candidate VOCs for inclusion in statistical models, with approximately the top 50 being retained. To develop the CPM, a logistic regression model with variable selection and importance assessment techniques will be fitted. Robust variable selection methods will be used, specifically the least absolute shrinkage and selection operator (LASSO) and elastic net. LASSO aids in selecting a more parsimonious model by shrinking less important predictor coefficients to zero, while elastic net combines the penalties of LASSO and Ridge regression, effectively managing correlated predictors.^14^

Elastic net is particularly beneficial when dealing with highly correlated variables, as it can select groups of related predictors, making it well-suited for multivariate datasets like VOC profiles. The best-performing model, determined through nested cross-validation (CV), will be advanced for further analysis.

In addition to the statistical methods, random forest and deep neural networks (DNNs) will be used to enhance model predictions. Random forest constructs multiple decision trees from different data subsets and combines their predictions, handling complex, non-linear relationships in the VOC data and identifying key VOCs that predict PDAC. DNNs, capable of capturing patterns in high-dimensional data, will be employed to model non-linear relationships in the VOC data. The DNN architecture will include a designed number of hidden layers and neurons, with regularisation techniques like dropout applied to prevent overfitting.

The model will be enhanced by assessing the additional diagnostic value of patient and clinical features (eg, family history of cancer, presenting symptoms), potentially improving its predictive power and clinical applicability.

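### Optimism is estimated and used to correct the performance plots, but no stated step applies the correction to the probabilities behind the decision rule and net benefit

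*Protocol article*

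**What the plan says.** Under Developing and reporting the CPM, many VOCs are screened, "with approximately the top 50 being retained", and a logistic model is fitted with LASSO or elastic net. Penalties are tuned by nested cross-validation. Optimism is estimated from 100 bootstrap resamples, and predictors selected in at least half of the bootstrap runs go forward. For the final model, "bias-corrected ROC (receiver operating characteristic) curves and calibration plots will be provided", and coefficients are reported with standard errors, and odds ratios with 95% confidence intervals.

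Under Outlier and missing data considerations, the imputation sensitivity analysis fits the CPM on a final predictor set in each dataset and pools by Rubin's rules.

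Under Derivation of diagnostic rules, "A clinical decision rule will be derived from probabilities of PDAC generated by the final CPM". The rule has three outcomes (referral, later review, discharge). Net benefit and decision curves are calculated across candidate thresholds, none of which is given as a number. The section mentions neither shrinkage nor recalibration, and it does not call the probabilities uncorrected.

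**The concern.** A bias-corrected calibration plot shows how far stated risks are from true risks, but it does not change the equation that gives a patient a risk. If the final equation is overfitted, its low risks are too low and its high risks too high, and the error in ratio terms is largest at the low end, where the rule would discharge.

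This matters wherever the rule uses a probability as a number. In net benefit and decision-curve analysis the threshold probability sets the exchange rate between false negatives and false positives. Miscalibrated risks mean that the elicited clinical costs are applied at the wrong true risk. Published coefficients would carry the same error to later users.

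The article's wording leans towards an unpenalised refit: a bootstrap vote on predictors, then standard errors, odds ratios, confidence intervals and Rubin pooling. Such a refit loses the shrinkage that the penalty supplied.

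**Working it through.** **Inputs from the article's Sample size section.**
- Cases: "The sample size of 205 PDAC cases was based on a target sensitivity of 85%, with 7% precision and 80% power".
- Controls: two further groups, each as large as the case group, which makes 615 with usable data.
- Recruitment: 771 once a 20% allowance for lost samples is added.
- Model: the CPM is expected to "achieve a minimum Cox-Snell R^2^ of 0.431 based on forty predictors".
- Discrimination: an assumed AUC of 0.86, with standard error 0.016.

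The number of VOCs screened, the thresholds and the calibration slope are not given.

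**1. The plan's own sizes.** With two-sided alpha 0.05 (assumed), n = (1.960 + 0.842)² × 0.85 × 0.15 / 0.07² = 204.2, so 205 cases. 3 × 205 = 615. 205/0.8 = 256.25, rounded up to 257, and 3 × 257 = 771. These reproduce. The PDAC fraction is 205/615 = 1/3, set by design.

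**2. Slope implied by the plan's inputs.** The expected-shrinkage criterion is n = P / [(S − 1) ln(1 − R²/S)].
- P = 40, R² = 0.431, S = 0.90: 40 / (0.10 × 0.652) = 613.7, against 615. The plan's figures therefore match a slope of about 0.90, which the article does not state.
- AUC 0.86 with a one-third case fraction and a binormal score implies R² of about 0.338. Then S = 0.868: 40 / (0.132 × 0.493) ≈ 615.
- With n = 615 and R² 0.431 or 0.338, 50 candidates give S = 0.88 or 0.84, 100 give 0.79 or 0.74, and 200 give 0.68 or 0.60.

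The formula describes a fit without a penalty.

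**3. From slope to risk error.** True risk = expit(a + S × logit(stated risk)), with a set so that mean stated risk is 1/3 (binormal score, AUC 0.86). Example: S = 0.90, a ≈ −0.05, stated 2%: 0.90 × (−3.892) − 0.05 ≈ −3.55, so true risk ≈ 2.8%, a ratio of 1.4. True over stated risk (the stated risks are illustrations, not proposed thresholds):

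| Slope | 1% | 2% | 5% | 10% |
|---|---|---|---|---|
| 0.90 (plan's inputs) | 1.5 | 1.4 | 1.3 | 1.2 |
| 0.868 (R² from AUC 0.86) | 1.7 | 1.6 | 1.4 | 1.2 |
| 0.80 (assumed) | 2.3 | 2.0 | 1.6 | 1.4 |
| 0.75 (assumed) | 2.8 | 2.3 | 1.8 | 1.5 |

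**4. Does the fitting route matter?** Simulation with n = 615, one third cases, AUC 0.86, 15 true markers, independent VOCs and 25 replicates (marker number and independence assumed):

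| Route | Slope in new patients | True/stated at 1–10% |
|---|---|---|
| 40 candidates, LASSO as fitted | 1.10 | 0.64–0.83 |
| 40 candidates, LASSO then unpenalised refit | 0.76 | 1.5–2.7 |
| 200 screened once to 50, LASSO as fitted | 0.79 | 1.4–2.3 |
| 200 screened once to 50, unpenalised refit | 0.55 | 2.0–6.1 |

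The route decides both size and direction. The simulated refit on 40 candidates does worse than the closed formula, so 0.87–0.90 is not a pessimistic reading of a refit.

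**5. Target setting.** The test is meant for primary care, where PDAC is far rarer than one in three. Moving from 1/3 to prevalence π multiplies the odds by [π/(1 − π)]/0.5: about 0.006, 0.020, 0.062 and 0.105 for assumed π of 0.3%, 1%, 3% and 5%. A stated 2% (odds 0.0204) then means about 0.01% to 0.21% even with no optimism. At slope 0.75 and π = 1%, the 4.6% true risk on the study scale (odds 0.048) becomes 0.048 × 0.0202 ≈ 0.10%. Resetting the intercept removes this error but not the slope error: at π = 1%, AUC 0.83 and slope 0.75, all assumed, a stated 0.25% is truly about 0.46%.

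**The case against.** The article nowhere says that the probabilities are uncorrected. It is a condensed text without its analysis plan, and the final CPM may already include a correction. LASSO and elastic net shrink coefficients, the penalties are tuned by nested cross-validation, and the sample size matches an expected shrinkage of 0.90. The order of description does not prove that screening sits outside the resampling. In the simulation, a LASSO kept as fitted on 40 candidates had slope 1.10, so low risks were overstated.

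A reader might infer that the plan definitely feeds uncorrected risks into the rule and that new patients near discharge carry about twice their stated risk. The documents do not support that. The refit is suggested, not stated. A factor of two needs a slope near 0.80 at a stated 2%, or near 0.70 at 5%, and neither slope nor threshold is given. For primary care patients, one-third case-mix probabilities used unadjusted would be far too high, not too low.

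Multiplying the linear predictor by a positive slope also preserves ranking, so a cut-off chosen purely from classification errors classifies the same patients the same way.

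All of this stands as a limit on the claim. What remains is that bias correction is assigned to two displays only, while the rule uses the model's probabilities as numbers. Penalisation cannot be relied on to close the gap: with 200 candidates screened once to 50, even the LASSO kept as fitted had slope 0.79.

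**Conclusion.** The point holds in a conditional form. The article estimates optimism and names a correction for plots, with no stated step that applies it to the equation behind thresholds and net benefit.

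If the voted predictors are refitted without a penalty, stated risks of 1–10% on the study's case mix would be understated by about 1.2–1.7 times at slopes of 0.90–0.87. With many VOCs screened, the factor would be about 2 (1.5 to 2.8) at an assumed slope of 0.75, and more below that. If a penalised fit is kept, the slope may be near or above 1, and little correction, or one in the opposite direction, is needed.

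These sizes rest on a binormal score, independent VOCs in the simulation, and assumed numbers of candidates and true markers. The harm is confined to absolute-risk thresholds, net benefit, decision curves and published risks. The design-fixed case fraction is a separate and larger error if probabilities are carried to primary care without an intercept reset; the two should not be left to offset each other by chance.

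**What to change.** In Developing and reporting the CPM, state that the final linear predictor is multiplied by its optimism-corrected calibration slope, from a bootstrap that repeats screening, tuning and selection in every resample. For a random forest or neural network, recalibrate on out-of-fold predictions. Publish the recalibrated coefficients, and say whether the final model is the penalised fit or a refit.

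In Derivation of diagnostic rules, state that absolute-risk thresholds, net benefit and decision curves use these recalibrated probabilities, with the intercept reset to a named target prevalence and its source. Re-estimating the intercept in the study data alone would keep the one-third fraction.

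Cost: a few sentences, a little more analysis work and no new data. Stated risks will usually become less extreme (more so if the slope exceeds 1). A slope near 1 leaves the coefficients unchanged, and ranking and error-based cut-offs are unaffected.

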## Methods and analyses

### Study design

VAPOR 1 is a UK prospective case–control study to construct a PDAC detection model based on VOCs in exhaled breath. The study involves the collection of breath at a single time point from eligible participants and is open to all National Health Service (NHS) trusts and diabetes education centres within the UK. The VAPOR 1 study is sponsored by Imperial College London and has obtained NIHR Clinical Research Network portfolio adoption to support study recruitment.

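### The planned three-action rule needs two cut-points, but the elicited cost and the named criteria fix only one, and the 85% sensitivity target is tied to neither

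*Protocol article*

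**What the plan says.** All of the rule's derivation is in the protocol article, under Derivation of diagnostic rules. The rule uses probabilities from the final prediction model, "with thresholds for referral for definitive testing, review within 6 months and discharge".

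The inputs and criteria named for it are:

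- Error costs: "Development of decision rules will consider the cost of missing a PDAC case and of incorrectly declaring PDAC in the control group".
- Net benefit: "The net benefit of the CPM will be calculated across a range of candidate thresholds", with decision curve analysis comparing the model "against the current standard of care of referring all symptomatic patients".
- A further criterion: "We will also consider the threshold which maximises the expected number of patients taking the test before misdiagnosis occurs". It carries a single weight, namely the cost "of a false negative relative to a false positive". That ratio is the only quantity that the section says will be elicited, from expert clinicians and the steering group.

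On the data, Study design states: "The study involves the collection of breath at a single time point from eligible participants". The only later outcome information described is histology within 3 months for patients awaiting resection of suspected PDAC (Definitions of study groups). Sample size sets 205 cases on a target sensitivity of 85% with 7% precision and 80% power. The internal validation paragraph reports sensitivity for each fold. Neither section says which cut-point the sensitivity belongs to.

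**The concern.** Each of the listed tools works on a choice between two actions. A cost ratio of false negative to false positive separates refer from not refer. Net benefit takes a threshold probability as its input and splits patients into test-positive and test-negative at that value; it does not by itself select a pair. The misdiagnosis criterion is worded for one threshold.

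A rule with a middle action needs more. A PDAC case placed in review is neither detected now nor discharged, and a non-case placed there is neither wrongly referred nor cleared. No cost is attached to either. The study cannot supply these costs later, because it does not observe what happens to a case whose referral is deferred.

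Two things are at stake. First, unless a fuller plan fixes the second cut-point, it would be chosen after the data are seen. Secondly, the sensitivity on which the study is sized can be read at either cut, and the two readings may lie far apart.

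**Working it through.** **1. The plan's own figures.** With p = 0.85, d = 0.07, 80% power and two-sided 5% (alpha is not stated, so assumed): n = (1.960 + 0.842)² × 0.85 × 0.15 / 0.07² = 204.2, rounded up to 205. With 20% attrition, 205/0.8 = 256.25, rounded up to 257, and 3 × 257 = 771. Both figures reproduce. The sizing rests on one binary sensitivity.

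**2. One ratio gives one cut-point.** With false-positive cost 1 and false-negative cost r, refer if p > 1/(1 + r). The documents give no r. Illustrative values:

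- r = 5: 0.167
- r = 10: 0.091
- r = 20: 0.048
- r = 50: 0.020

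**3. What three actions need.** Let D be the cost of a PDAC case placed in review and V the cost of a non-case placed in review, on the same scale. Expected costs at probability p are:

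- refer: (1 − p) × 1
- review: p × D + (1 − p) × V
- discharge: p × r

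Equating neighbours gives:

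- refer/review odds = (1 − V)/D
- review/discharge odds = V/(r − D)

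Both cut-points contain D and V. The review band exists only if V/(r − D) < (1 − V)/D, which simplifies to D/r + V < 1.

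**4. Same elicited ratio, different cut-points** (all costs assumed). Take r = 20 and V = 0.2.

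- D = 10: upper odds 0.8/10 = 0.08, so 7.4%; lower odds 0.2/10 = 0.02, so 2.0%.
- D = 4: upper odds 0.8/4 = 0.20, so 16.7%; lower odds 0.2/16 = 0.0125, so 1.2%.

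At r = 10, with D/r and V each from 0.1 to 0.5, the lower cut runs from 0.011 to 0.091 and the upper from 0.091 to 0.474. At D/r = V = 0.5 both equal 0.091 and the band is empty.

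**5. Effect on sensitivity.** Inputs: AUC 0.86 and 205 cases (Sample size). Assumed: an equal-variance binormal model, the 85% placed at the lower cut, and the upper-cut specificity. The separation is √2 × Φ⁻¹(0.86) = 1.528. At 85% sensitivity the cut is 1.528 − 1.036 = 0.491, with specificity Φ(0.491) = 68.8%. Referral-only sensitivity is Φ(1.528 − Φ⁻¹(specificity)).

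| Upper-cut specificity (assumed) | Referral-only sensitivity | Cases in review, of 205 | Controls in review |
|---|---|---|---|
| 80% | 75.4% | about 20 | 11.2% |
| 85% | 68.8% | about 33 | 16.2% |
| 90% | 59.7% | about 52 | 21.2% |
| 95% | 45.3% | about 81 | 26.2% |

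The two readings differ by 85 − 75.4 = 9.6 to 85 − 45.3 = 39.7 points, against a design precision of 7. If the 85% belongs to the upper cut instead, a lower cut at 90% or 95% sensitivity has specificity 59.7% or 45.3%.

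**The case against.** The strongest reply is that the article's list is open. It considers costs, computes net benefit over a range of thresholds and adds a further criterion, and the elicited ratio is attached only to that last one. One cut-point could come from one criterion and the second from another. How each is chosen may stand in the full protocol or analysis plan, which are not shown, and an article may leave such detail to them.

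Much of this stands, and it rules out three stronger readings that a reader might infer:

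- That the review tier cannot be derived from one breath sample. Two cut-points can be placed on one predicted probability. The single time point only prevents evaluation of what review achieves, and the article does not claim to evaluate that.
- That the second cut-point is arbitrary. The text supports only that the stated criteria do not fix it.
- That the rule's sensitivity is undefined, or that review will be counted as a positive test. Sensitivity is computable at each cut, bias-corrected ROC curves are promised, and nothing says how review is counted. The target is ambiguous, no more.

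What the reply does not remove is the mismatch within the section. The article names both the three actions and the quantity to be elicited, and that quantity is insufficient for the actions. Costs not asked for in the elicitation cannot be recovered from the study data.

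**Conclusion.** The point holds in this limited form. A three-action rule needs two cut-points; the elicited ratio fixes one, and the other named measures are framed for two actions. The 85% target is tied to neither cut. No arithmetic in the plan is wrong: 205 and 771 both reproduce.

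The ambiguity is worth about 10 to 40 points of sensitivity, or about 20 to 81 of 205 cases. That size rests on the equal-variance binormal model, on placing the 85% at the lower cut, and on upper-cut specificities of 80% to 95%, none of which the documents give. The cost examples are likewise assumed. They show only that one and the same ratio is compatible with quite different pairs of cut-points. The matter should be settled before the elicitation is run.

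**What to change.** Keep the tiers as the sponsor defines them.

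- Add two relative costs to the planned elicitation: a PDAC case placed in review, and a non-case placed in review.
- Derive both cut-points by minimum expected cost: refer/review odds = (false-positive cost − non-case review cost)/deferred-case cost; review/discharge odds = non-case review cost/(false-negative cost − deferred-case cost). State that the review band is empty if the cuts meet or cross.
- Apply these to probabilities on the target-population scale. The sample holds 205 cases to 410 controls (odds 0.5), so model odds must be multiplied by [π/(1 − π)]/0.5, where π is the prevalence in the intended population. The article gives no π; state the value used and a range.
- State which cut-point carries the 85% target. Report sensitivity, specificity and net benefit at both cuts, with the shares of cases and of controls in review.
- State that the outcome of review cannot be evaluated in this design.

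The cost is two further questions in an elicitation already planned, plus some wording in the analysis plan. The downside is that referral-only sensitivity, shown beside sensitivity at the lower cut, will be the lower of the two.
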